### Sample selection criteria

The target population is the community-dwelling family caregivers of PWD. Inclusion criteria are as follows: 1) those aged 18 years or older; 2) blood or by-marriage relatives (e.g., spouses, siblings, children, and grandchildren) of a person who has been clinically diagnosed with dementia, regardless of its types, with these relatives taking on the caring responsibilities ranging from physical aids to emotional support in the form of transportation, financial assistance, personal hygiene, and decision-making; 3) providing most of the daily care and support for PWD (daily contact for at least 4 h); and 4) able to speak Cantonese (for understanding all the teaching materials and instructions).

Caregivers will be excluded if they: 1) are practicing or recently learned meditation, mindfulness activities, and/or relaxation training in the past 6 months; 2) are diagnosed with a mental disorder such as bipolar disorder, schizophrenia, dementia, or depression in an acute stage; 3) are taking anticonvulsants or any kind of psychotropic drugs starting within the past 4 weeks which could be regulated or adjusted during the intervention period and thus the mental state might not be stable during the study; and/or 4) are identified with self-reported suicidal thought or drug abuse in the past 6 months.

The family caregivers receiving different types of support (other than MBI) such as domestic helpers, respite care, old age placement, old age allowance, meal delivery, or other financial support from the government will not be excluded, but the information will be reflected in the demographic data.

### Sample size

The sample size estimation was based on the primary outcome (stress). In the previous systematic review, the effect size of the MBCT for stress reduction was found to have Cohen’s *d* of 0.57 immediately after the intervention [15]. However, the intervention protocol is further modified and its duration is shortened in this proposed study. A conservative effect size Cohen’s *d* of 0.4 was adopted to detect the mean difference in stress reduction between the intervention and control groups. Based on the power analysis using the software G***Power 3.1 on repeated-measures analysis of variance (ANOVA), a sample size of 84 participants will be needed to achieve 80% power at a two-sided 5% significance level. According to the results of the feasibility study in Hong Kong, an attrition rate of 4% was found [16]. By adopting a more conservative estimation of the attrition rate of about 10%, the estimated sample size is at least 100 for this proposed study, 50 per group.

### Recruitment procedure

A convenience sampling method will be used to recruit participants. An invitation email will be sent to the three nongovernmental organizations providing elderly care services for PWD and their caregivers. If there are more than enough participants recruited from different centers, an equal proportion of participants will be randomly selected from different centers to maximize the diversity of the caregivers living in different districts.

### Randomization and blinding

The eligible participants will be randomized into the two groups (modified MBCT or social interaction and routine education (SIRE)) following an allocation concealment mechanism. To ensure equal sample sizes (1:1) in the modified MBCT and SIRE, the allocation of participants will be performed using a block randomization method and computer-generated numbers by an independent research assistant who will not be involved in the recruitment, assessment, or delivery of the intervention. The procedure and treatment allocation will be blinded to the investigators and outcomes assessors. The interventionists will be blinded to all the assessment results. The subjects will be told about their group assignment during the first session of the intervention via a sealed envelope.

### Interventions

#### The MBCT group

A group-based, 10-week, seven-session modified MBCT will be adopted in the intervention group (Table 1). Compared with the original MBCT protocol [14], the modified MBCT protocol in this pilot study has the following changes:Integrating the contents of the third and fourth sessions into one session and abridging the full-day retreat (rationale: to promote the feasibility of complying with the intervention required for the caregivers). A study with a similar number of sessions of MBI demonstrated a moderate to large effect size on psychological outcomes in patients with cancer, which supports that the intervention of the present program may be sufficient [17].Biweekly session for the last three sessions (rationale: facilitate the caregivers to apply mindfulness in daily lives and promote continuous home practice).Telephone follow-up for the last three sessions (rationale: to monitor the progress of practicing mindfulness and answer simple questions or technical problems such as playing the CD).Content about relapse prevention for a major depressive disorder, such as territory of depression in session 4 and relapse signature in session 5 in the original MBCT, will be replaced by psychoeducation about family caregiving stress and mindful communication (rationale: since MBCT was originally designed for people with recurrent depression, some content on relapse prevention for a major depressive disorder, such as territory of depression in session 4 and relapse signature in session 5, may not be applicable to caregivers of PWD). From the literature review, the family caregivers and the PWD usually have a conflict during their communication [18]. Mindful communication is an activity developed from the MBSR program and helps the participants to be mindful in the interactions with others including their family members. Several studies have adopted it for family caregivers of people with different diseases to improve their communication [19, 20].

**Table 1 Tab1:** Modified mindfulness-based cognitive therapy (MBCT) program

Session	Main theme	Content	Home practice
1	Awareness and automatic pilot	➢ Establish the orientation of the class ➢ The Raisin exercise (eating meditation) ➢ 13-min body scan ➢ Feedback and discussion of exercise	➢ 45-min body scan for 6 out of 7 days ➢ Mindfulness of a routine practice
2	Living in our head	➢ Practice review ➢ Thoughts and feelings exercises ➢ 45-min body scan ➢ Brief mindfulness of breathing	➢ 45-min body scan for 6 out of 7 days ➢ 10 min of mindfulness of breath for 6 out of 7 days ➢ Pleasant experience calendar (one example daily) ➢ Mindfulness of a routine practice
3	Gathering the scattered mind	➢ Practice review ➢ Focus on unpleasant experiences exercises ➢ Seeing and hearing practice ➢ Sitting meditation (awareness of breath and body and responding to painful sensations) ➢ 3-min breathing space ➢ Mindful stretching and breath meditation ➢ Mindful movement	➢ Stretching and breathing meditation on days 1, 3, and 5 ➢ 40-min mindful movement on days 2, 4, and 6 ➢ Unpleasant experience calendar (a different experience each day) ➢ 3-min breathing space, three times daily
4	Recognizing aversion and allowing	➢ Practice review ➢ Seeing and hearing practice ➢ Mindful communication ➢ 3-min breathing space ➢ Mindful walking ➢ Sitting meditation (awareness of breath, body, and sounds, then how we relate to our experience through the reaction)	➢ Sitting meditation, 6 out of 7 days ➢ 3-min breathing space (three times a day) ➢ 3-min breathing space—responsive (whenever notice unpleasant feelings)
5	Thoughts are not facts	➢ Practice review ➢ Sitting meditation ➢ Mood, thoughts and alternative viewpoints exercise ➢ 3-min breathing space (responsive) ➢ Psychoeducation in family caregiving stress	➢ Select a guided meditation to practice at least 40 min per day ➢ 3-min breathing space (three times a day) ➢ 3-min breathing space—added instructions (whenever notice unpleasant feelings)
6	Take care of myself	➢ Practice review ➢ Sitting meditation with breath, body, sounds ➢ Activity and mood exercise ➢ Identifying habitual emotional reactions to difficulties ➢ 3-min breathing space (responsive)	➢ 3-min breathing space (three times a day) ➢ 3-min breathing space—added instructions (whenever notice unpleasant feelings) ➢ Select from all different forms of practice and apply them on a regular basis ➢ Develop action to be used in the face of lowered moods
7	Maintaining and extending new learning	➢ Practice review ➢ 45-min body scan ➢ Looking forward exercise ➢ Preparing for the future exercise	

The modified MBCT protocol was reviewed by an expert panel including mindfulness interventionists, nurses experienced in dementia care, and clinical psychologists to validate the contents of the protocol. Consensus among the experts on the contents of the MBCT was achieved through discussion of their suggestions. The protocol was also tested in the prior feasibility study and further modified for this main study.

#### Group size

Each group will have 15–20 participants to maintain sufficient group interactions between the MBCT instructor and all of the participants. A previous study indicated that the group effect accounted for 7% of the variability in the psychological outcomes (measured by the General Symptom Index) and that the group effect can be regarded as a booster in MBCT to improve the psychological outcomes [21]. In previous clinical trials on MBCT for people with recurrent depression, the group size was similar and varied from 12 to 14 [22–24]. The target population of our study is family caregivers without major depression. From the focus group of our prior feasibility study, most of the participants were satisfied with a group size of around 18 and indicated that they could discuss and share different caring experiences with their group colleagues [16]. There was also a significant change in mindfulness level immediately after the MBCT in the feasibility study, which indicated that most of the participants could master the skills of the mindfulness activities. Moreover, a smaller mindfulness group of 8 to 10 participants would not be cost-effective enough to accommodate or manage an increasing number of caregivers of PWD. In view of the previous literature and findings from the feasibility study, 15 to 20 participants were adopted as our group size.

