#### Control group (SIRE on dementia care)

The participants of the control group will be provided with chances to socialize and interact with other participants via the SIRE program. The SIRE program has been developed for this study and the aim is to control the socialization and interaction effect as it may mask the effects of the modified MBCT in stress reduction, making it difficult to draw a meaningful conclusion about the effectiveness of the modified MBCT for family caregivers of PWD. The SIRE program consists of seven sessions, with the same group size, duration, and frequency of sessions as the MBCT group, including education sessions on dementia care, caregiver skills training, and group sharing on caregiving tasks. The program will be delivered by an experience nurse in dementia care.

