### Data analysis plan

IBM SPSS 23.0 software will be used for the data analysis. The Kolmogorov–Simonov test will be used for checking normality. To ensure the similarity of the subjects in the two groups (modified MBCT and SIRE) at baseline, the demographics, adherence rate, frequency of mindfulness practice, and the outcome measurements will be compared by using a *t* test for continuous variables and a Chi-square test for categorical variables. Covariates will be controlled in the main analyses if a significant difference of variables is found at baseline. Both per-protocol (PP) and intention-to-treat (ITT) analyses will be performed. In the PP population, we will include the subjects who attend > 70% of the intervention sessions. A sensitivity test will be performed to compare the differences between the ITT and PP results. The aim of conducting both ITT and PP analyses is to uncover factors affecting the use and effectiveness of the modified MBCT, such as noncompliance and acceptability [48].

Descriptive statistic will be used to analyze the recruitment rate, attrition rate, duration, patterns, and consistency of the participants practicing mindfulness to indicate the acceptability of the MBCT. Mixed multivariate modeling (MANOVA) tests will be adopted to investigate the between-group effect (groups: modified MBCT and SIRE), the within-group effect (times: T0, T1, and T2), and the interaction time effect of group by time effect (group × time) on all of the outcome variables including PSS, HADS-A, CESD, ZBI, BRS, NPI-Q, and SF-12v2, and the process indicator (FFMQ). Correlation checking by Pearson’s product moment correlation of all the psychological outcomes including PSS, HADS-A, CESD, ZBI, BRS, NPI-Q, SF-12v2, and the process indicator (FFMQ) at baseline will be performed. If the correlation is too strong (Pearson’s *r* > 0.6), which may result in multicollinearity and violation of the assumption of mixed repeated MANOVA, then two-way repeated ANOVA and Bonferroni’s adjustments will be adopted to prevent a type I error [49]. Post-hoc pairwise comparisons using Tukey’s Honestly Significant Difference (HSD) will be performed to examine the significant difference in the outcomes.

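### Both arms are treated in groups of 15–20 and the protocol cites a 7% group effect, but the sample size and the analysis treat the 100 caregivers as independent

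*Protocol article*

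**What the plan says.** All of this is in the Methods of the protocol article.

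- **Randomization and blinding:** individual caregivers are allocated 1:1 in blocks.
- **Group size:** for the MBCT arm, "15 to 20 participants were adopted as our group size". The same section states that "A previous study indicated that the group effect accounted for 7% of the variability in the psychological outcomes". The measure there was the General Symptom Index, and the protocol presents the effect as a benefit of MBCT.
- **Control group:** SIRE is run "with the same group size, duration, and frequency of sessions as the MBCT group".
- **Intervention fidelity** and **Control group:** one interventionist delivers all modified MBCT sessions, and one nurse is named for SIRE.
- **Sample size:** a Cohen's d "of 0.4 was adopted to detect the mean difference in stress reduction between the intervention and control groups". From a G*Power repeated-measures ANOVA, "a sample size of 84 participants will be needed to achieve 80% power at a two-sided 5% significance level". The only allowance added is "a more conservative estimation of the attrition rate of about 10"%, giving at least 100, 50 per arm.
- **Data analysis plan:** "Mixed multivariate modeling (MANOVA) tests will be adopted to investigate the between-group effect", the time effect and their interaction. If baseline correlations between outcomes exceed 0.6, two-way repeated ANOVA with Bonferroni adjustment replaces it. The groups in this model are the two arms; no term for the delivered therapy group appears.

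**The concern.** This is an individually randomised trial in which treatment is given in groups. Randomisation removes clustering at T0. It does not prevent clustering during treatment, when about 16–17 people meet for seven sessions and influence one another. The dependence therefore enters at T1 and T2, which is inside the arm × time term that tests the primary hypothesis.

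MANOVA and repeated-measures ANOVA allow for correlation within a person over time but assume that different people are independent. If people in one group are positively correlated, the MBCT–SIRE difference has a larger variance than the model reports. Confidence intervals are then too short and the test rejects too often. The Conclusion section says that significant benefits would support MBCT as a standard supportive intervention, so a false positive would matter.

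An unseen analysis plan cannot simply be assumed to cover this. The article itself fixes the sample-size method and the model effects on an independence basis, while citing evidence against independence.

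**Working it through.** **Inputs from the protocol.** 50 per arm; groups of 15–20, so about 3 groups per arm with mean size m = 50/3 = 16.7; d = 0.4; two-sided 5%; 80% power; N = 84 before attrition; cited group effect 7%.

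**Assumptions.** The ICC of PSS is not given. The cited 7% is tried as the ICC, with 0.01–0.10 as a range. The within-person correlation r is not given either; 0.3–0.7 is used.

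**1. The plan's own figure.** With f = d/2 = 0.2 and three visits, the noncentral F gives:

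| Test | r | Smallest N for 80% | Power at N = 84 |
|---|---|---|---|
| Interaction | 0 | 82 | 0.811 |
| Between-arm | 0.1 | 82 | 0.817 |
| Interaction | 0.5 | 42 | 0.984 |
| Between-arm | 0.5 | 134 | 0.602 |

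So 84 can be approached under an unstated correlation and is not shown to be wrong. No design effect is needed to reach it. 84/0.9 = 93.3, so 100 covers the stated attrition and leaves little for clustering.

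**2. Design effect.** DE = 1 + (m − 1) × ICC. At ICC 0.07:

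- m = 15: 1 + 14 × 0.07 = 1.98
- m = 16.7: 1 + 15.7 × 0.07 = 2.10
- m = 20: 1 + 19 × 0.07 = 2.33

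At m = 16.7 the effective sample is 100/2.10 ≈ 48. The unadjusted standard error is 1/√2.10 = 0.69 of the true one.

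**3. Type I error of one unadjusted 5% test.** α = 2 × [1 − Φ(1.96/√DE)].

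| ICC | Clustering | α at m = 16.7 |
|---|---|---|
| 0.01 | both arms | 6.8% |
| 0.02 | both arms | 8.7% |
| 0.05 | both arms | 14.2% |
| 0.07 | both arms | 17.6% (16.4% at m = 15, 19.9% at m = 20) |
| 0.10 | both arms | 22.1% |
| 0.07 | MBCT arm only | 11.5%, with average DE (2.10 + 1)/2 = 1.55 |

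**4. Simulation of the arm × time F test.** Groups of 17, 17 and 16 per arm, with the group effect present at T1 and T2 only and ICC 0.07 in both arms. Rejection was about 14% at r = 0.3, 17–18% at r = 0.5 and 23–27% at r = 0.7. The spread reflects the variance set-up and simulation error. A t test on the six group means held 5.0%.

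**5. Bonferroni fallback.** Over seven outcomes the nominal level is 0.05/7 = 0.7%, with z = 2.69. At DE 2.10 the actual level is 2 × [1 − Φ(2.69/√2.10)] ≈ 6%.

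**6. Power with clustering respected.** For a baseline-adjusted comparison at one visit, with r = 0.5, three groups per arm and 4 df: SE = √{2 × [ICC/3 + (1 − r² − ICC)/50]}.

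- ICC 0.02: √[2 × (0.0067 + 0.0146)] = 0.206; 0.4/0.206 = 1.94; power ≈ 32%.
- ICC 0.07: √[2 × (0.0233 + 0.0136)] = 0.272; 0.4/0.272 = 1.47; power ≈ 21%.

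With ICC 0 and 97 df the same comparison has SE √(2 × 0.75/50) = 0.173 and power of about 63%. So part of the gap to 80% comes from the choice of comparison; the fall from about 63% to 32% or 21% is the effect of clustering and of having only six groups.

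**The case against.** The strongest objection concerns size. The 7% comes from another study, on the General Symptom Index rather than PSS, and the protocol does not say how it was estimated. It is cited as a feature of MBCT, and nothing in the documents supports the same value in SIRE. A reader might infer that the trial's 5% test runs at 17%. The documents do not support that as a fact: it is one point in a range that falls to about 7% at ICC 0.01.

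The calculation also covers one univariate PSS test at 5%. The first-line analysis is a MANOVA over several outcomes, for which no figure was computed. The Bonferroni fallback would run at about 6%, which is near 5% but far above its own nominal 0.7%.

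A reader might also blame a shared instructor. That does not hold. One interventionist delivers all MBCT sessions and one nurse is named for SIRE, so the instructor is constant within each arm and creates no differences between groups in the same arm. What remains is peer discussion and group dynamics.

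These points limit the magnitude. They leave the omission itself standing: the word mixed in the analysis plan does not supply a therapy-group term, and individual randomisation does not protect the post-baseline comparison.

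**Conclusion.** The concern holds. The protocol delivers both arms in groups and cites evidence that groups affect outcomes, then fixes a sample size and model that assume independence. Any positive ICC makes the reported standard errors too small and removes the basis for the 80% power.

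Confidence is high for the omission and conditional for its size. For a univariate PSS test at nominal 5%, type I error is about 16–20% if 7% is the PSS ICC in both arms, and about 18–25% in the simulated interaction test at r = 0.5–0.7. It is about 11.5% if only MBCT clusters, and about 7–9% at ICC 0.01–0.02. These figures assume about three groups of equal or nearly equal size per arm.

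**What to change.** 1. Record the group in which each participant was actually treated.
2. Make the primary PSS model a linear mixed model with a random effect for therapy group nested in arm (acting after baseline), a participant-level covariance over visits, and Satterthwaite or Kenward–Roger degrees of freedom.
3. Report the estimated ICC with its interval, and say that about six groups estimate it poorly; an estimate of zero will be common and is not evidence of no clustering.
4. Replace the 80% power sentence with one that gives the group size, the assumed ICC range (0.02–0.07) and the resulting power: about 32% to 21% for d = 0.4 with three groups per arm and r = 0.5.

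The cost is one recorded variable and revised analysis wording, with clearly wider intervals and a much lower stated power. No extra participants are needed to make the error bars honest. The change does not restore 80% power: that would take more groups, since adding people to the same groups helps little, and recruitment began in May 2018.

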#### Duration of sessions

The intervention will contain seven sessions and each session will last for about 2 h. A study with a similar number of MBI sessions demonstrated a moderate to large effect size on psychological outcomes in patients with cancer, which supports that the intervention of the present program may be sufficient [17]. The design of the original MBCT contained eight sessions with a 1-day retreat. Since family caregivers of PWD take up several roles and tasks in their daily life, most of the previous studies eliminated the retreat session to increase the adherence [20, 25, 26]. In our prior feasibility study, a number of the caregivers indicated that it was difficult to find time to join the whole-day retreat. Therefore, we eliminated the retreat session and combined sessions three and four in our feasibility study to shorten the duration. Eventually, the entire program contained seven sessions. Even though the length of each session was shortened in the feasibility study, a significant increase in the mindfulness level measured by the Five Facet Mindfulness Questionnaire (FFMQ) was identified, together with significant improvements in the psychological outcomes of the participants, immediately after the MBCT program. FFMQ is one of the most comprehensive and frequently used measures assessing individual differences in mindfulness skills and its psychometric property is described below. Therefore, we have adopted the same duration for the sessions here as in the feasibility study [16].

#### Frequency

The intervention will be set as weekly for the first four sessions and bi-weekly for the last three sessions. Since the participants were taught about the major components and skills of mindfulness in the first four sessions, the family caregivers could apply and practice the skills in their caregiving tasks. The caregivers return 2 weeks after the first four sessions to continue the bi-weekly sessions and they can then share more about the difficulties in applying mindfulness skills over the past 2 weeks. Compared with the original design of the MBCT protocol, the caregivers have more chances to practice in their daily lives which may facilitate the caregivers to develop a habit of daily mindfulness practice.

